## 5. Measures

**Anthropometrics, Body Fat, and Blood Pressure:** For both children and parents, weight will be measured using a SECA (model 869) digital scale to the nearest 0.1 kg, and height will be measured using a wall-mounted stadiometer to the nearest 0.1 cm. BMI ( $\text{kg/m}^2$ ) and BMI percentiles for CDC age- and gender-specific values will be determined using EpiInfo 2005, (CDC, Atlanta, GA). Waist circumferences (WC) will be measured and recorded to the nearest 0.1 cm. Body composition will be assessed using Bioelectrical Impedance with the Tanita Body Fat Analyzer (model TBF 300). Blood pressure will be obtained in duplicate with an automatic cuff according to recommendations of the American Heart Association. A skin carotenoid scan will be completed of the finger, which will take approximately 20 seconds. This is a noninvasive device that measures carotenoids in the skin to assess fruit and vegetable consumption. The device uses a technique called reflectance spectroscopy, which involves shining a light on the skin of one finger to measure carotenoids in the skin which gives us an objective measures of vegetable intake.

Parental height, weight, body fat, WC, and blood pressure will be collected at first and last family workshop (expecting a subsample only). Therefore we will ask self-reported height and weight in questionnaire packets.

**Dietary Intake:** The Block Food Screener for Ages 2-17, 2007 will be used to measure dietary intake on all children. This 41-item screener asks about food eaten "yesterday," and was designed to assess children's intake by food group, with a specific focus on fruit and fruit juices, vegetables, potatoes (including and excluding French fries), whole grains, meat/poultry/fish, dairy, legumes, saturated fat, and "added sugars" (in sweetened cereals, soft drinks, and sweets). This screener was designed for self-administration by children with the assistance of an adult and takes ~10 minutes to complete. The screener was developed and adapted from the Block Kids 2004 Food Frequency Questionnaire (FFQ) and was recently validated against this FFQ in 2,376 primarily Hispanic children (8 y). We will also collect 24-hour diet recalls in a subset of children (n=500, half in the intervention and half in the control group). Trained interviewers will collect three 24-hour recalls using the multiple pass technique by telephone (making sure to obtain 1 weekend and 2 weekdays) within 10 days of each testing visit. [name] has extensive experience training students/staff to collect and enter FFQs and 24-hour recalls. UT-Austin has a large pool of undergraduate dietetics students who will be trained to assist with collection of these recalls as part of their research credit hours. All recall data will be analyzed using the Nutrition Data System for Research (NDS-R 2014, University of Minnesota). Dietary intake for all parents will be measured using Block Fat/Fruit/Vegetable/Fiber screener, which is a validated 10-item screener that is available in English or Spanish.

**Demographic and Dietary Psychosocial Measures:** Demographic information including age and ethnicity will be obtained via a questionnaire. To ascertain socioeconomic status, we will ask students whether their family uses a computer at home and whether their mother has her own car, and we will ask parents to report income level. Parents will fill out a brief medical history form for their child and themselves to rule out exclusion criteria mentioned above. Children and parents will complete the Motivation for Fruit and Vegetable Intake, Gardening, and Cooking Scale, which has been adapted from the Treatment Self-Regulation Questionnaire (TSRQ). We will measure FV preferences as well as self-efficacy to garden/eat/prepare FV in both the child and parent using existing questionnaires that have been developed and validated with pediatric populations. The Child Eating Behavior Questionnaire (CEBQ), which is a validated parent-report instrument to assess obesogenic eating behaviors in children, will also be administered. Physical activity (PA) information will be obtained on the child via a 3-day physical activity recall (3-Day PAR), a semi-structured interview that estimates an individual's time spent in PA, strength, and flexibility activities during the three days prior to the interview. This survey has been validated for PA assessment in children. All parent questionnaires will be available in both English and Spanish, and written at a 3rd grade reading level.

## Accelerometers

Children will be asked to wear accelerometers throughout the day during the weeks of data collection. These will be used to record their daily physical activity levels and to have a quantitative measure of how much activity they incur during regular classes, recess, etc.

With regard to wearing accelerometers, children will wear them from the start of the school day until the end of the school day for a 5-day period. From previous projects, it has been seen that children enjoy wearing the accelerometers and are excited to have their step counts recorded. Any discomfort about wearing the accelerometer on a belt around the waist is offset by the excitement factor of wearing one. If a child states they are uncomfortable wearing one, they will not be required to wear an accelerometer.

**Time on Task:** Children will be observed for time-on-task measures during designated class times by trained project staff. The observers will sit or stand in a corner of the classroom and will not interact with the teacher or the students. The observers will be in the classrooms for about 15-20 minutes at a time and then leave quietly. Observers will write field notes on whether the student is staying on task throughout a portion of a lesson. Students are used to having classroom visitors enter and exit the classroom as part of the regular school day, and thus are used to visitors in the rooms. No observation data will be shared with the students or the teachers to maintain confidentiality of observations. Little to no disruption will occur to the classroom setting as the regular lessons are taught.

**Fasting Blood Sample:** Certified phlebotomists will perform the fasting blood draws on students first thing in the morning before school starts at the schools at baseline and at the end of the school year. Blood draws will occur on school campus in the school health clinic or another designated sterile area. A total of 48 ml of blood will be drawn at baseline and 9 months later at post-testing. Students with parental consent and assent will participate in the blood draw and receive a cash incentive (\$20 per draw). Students who do not assent to participate in the blood draw will still be allowed to participate in the Sprouts program and other evaluation measures. A reminder blood draw letter will be sent out for post evaluations. We will also send a normal diabetes test to all blood draw participants who do not have elevated glucose levels. Fasting blood will be drawn to assess glucose, insulin, lipids, and adipocytokines. Blood samples will be spun, aliquotted, frozen, and transported to the UT campus for assaying. Glucose will be assayed using a Yellow Springs Instruments analyzer (Yellow Springs, OH) and insulin using an automated enzyme immunoassay system analyzer (Tosoh Bioscience, Inc. San Francisco, CA). Homeostatic model assessment (HOMA-IR) will be used as a measure of insulin resistance. Total cholesterol, high-density lipoprotein cholesterol (HDL), and triglyceride levels will be measured using the Vitros chemistry DT slides (Ortho Clinical Diagnostics Inc., Rochester, NY); low-density lipoprotein (LDL) will be calculated using the Friedwald formula. Adipocytokines (i.e., leptin, adiponectin, interleukin-6) will be measured using the Millipore Multiplex assay kit. Metabolic syndrome will be calculated using a combination of Cruz et al. and Cook et al. definitions. All children who participated in the fasting blood draw will be mailed a copy of their diabetes screening results and those with elevated glucose levels (in the abnormal or T2D range) will be contacted via telephone by [name] (Co-I on this study) to explain the test results and be referred immediately to a health clinic for follow-up. However, these children will still be allowed to participate in the study.

**Sustainability Measures:** During the Sprouts intervention and sustainability year, we will collect pilot data on sustainability strategies being implemented in both the intervention and control schools. Structured interviews and audio-recorded meeting data will be conducted with GLC members to document member information, leadership structure, meeting times/places, how the garden was designed/built, workshops offered/attended, fundraising and media events, types of produce harvested, produce use and distribution plans, community resources leveraged, barriers and future action plans. Structured interviews, surveys and audio-recorded meetings will be conducted with teachers, principals, administration staff, GLCs, and district

directors and staff to evaluate various aspects of the program including: a) use and maintenance of garden; b) successful and unsuccessful components/strategies implemented to sustain program; and c) additional material/resources/training requested and/or needed. We will also conduct observations of schools to assess whether the garden is being maintained and examine what aspects of the program are still being maintained and strategies used to sustain the program (see Appendix for structured interview and focus group consent form).

**Data Collection:** Some study data will be collected and/or managed using REDCap (Research Electronic Data Capture). REDCap is a secure, web application designed to support data capture for research studies, providing user-friendly web-based case report forms, real-time data entry validation (e.g. for data types and range checks), audit trails and a de-identified data export mechanism to common statistical packages (SPSS, SAS, Stata, R/S-Plus). REDCap also provides a powerful tool for building and managing online surveys. The research team can create and design surveys in a web browser and engage potential respondents using a variety of notification methods. The system was developed by a multi-institutional consortium, which includes University of Texas at Austin and was initiated at Vanderbilt University. The database is hosted at the Population Research Center, which will be used as a central location for data processing and management. The PRC server has been cleared for Category-I data collection by UT's Information Security Office. Network transmissions (data entry, survey submission, web browsing, etc.) in REDCap are protected via Secure Sockets Layer (SSL) encryption. REDCap data collection projects rely on a thorough study-specific data dictionary defined in an iterative self-documenting process by all members of the research team with planning assistance from the PRC. The iterative development and testing process results in a well-planned data collection strategy for individual studies. REDCap provides a secure, web-based application that is flexible enough to be used for a variety of types of research, provide an intuitive interface for users to enter data and have real time validation rules at the time of entry.

**Sample Size and Power Analysis: For Aim 1:** We estimated the power of this study for children using pilot data from five primary variables from LA Sprouts: vegetable intake (serv/d), BMI z-scores, waist circumference, fasting glucose (mg/dL) and fasting insulin ( $\mu$ U/ml). We estimated minimum sample size using several effect sizes on the difference between intervention and control group on the change of

**Table 2:** Minimum number of schools required evaluating the differences in the effect sizes between

|                                                                                               |             | Children (cluster average size of n=127 for diet, waist, BMI z-scores and 60 for glucose/insulin values per school) |                 |                  |                     |                  | Parents (cluster average size of n=64 per school) |                 |
|-----------------------------------------------------------------------------------------------|-------------|---------------------------------------------------------------------------------------------------------------------|-----------------|------------------|---------------------|------------------|---------------------------------------------------|-----------------|
|                                                                                               |             | Vegetable Intake                                                                                                    | Blood Glucose   | BMI Z score      | Waist circumference | Insulin          | Parents: Vegetable - Intake or Availability       |                 |
| Type I error level                                                                            |             |                                                                                                                     | ICC=0.071       | ICC=0.001        | ICC=0.002           | ICC=0.019        | ICC=0.554                                         | ICC=0.071       |
|                                                                                               |             |                                                                                                                     | $\sigma^2=0.08$ | $\sigma^2=40.86$ | $\sigma^2=0.05$     | $\sigma^2=0.005$ | $\sigma^2=30.41$                                  | $\sigma^2=0.08$ |
|                                                                                               | effect size |                                                                                                                     | 0.500           | 2.133            | -0.065              | -0.020           | -12.000                                           | 0.510           |
| 0.05                                                                                          | power       | 0.8                                                                                                                 | 12              | 6                | 4                   | 12               | 14                                                | 12              |
|                                                                                               |             | 0.9                                                                                                                 | 16              | 8                | 6                   | 16               | 20                                                | 16              |
| 0.01                                                                                          | effect      | 0.8                                                                                                                 | 18              | 8                | 6                   | 18               | 24                                                | 18              |
|                                                                                               |             | 0.9                                                                                                                 | 22              | 10               | 8                   | 22               | 30                                                | 24              |
| ICC: intraclass correlation coefficient; $\sigma^2$ : variance within schools from pilot data |             |                                                                                                                     |                 |                  |                     |                  |                                                   |                 |

ICC: intraclass correlation coefficient;  $\sigma^2$ : variance within schools from pilot data

measurements from baseline to end of study. We assumed that a cluster average size of 127 children per school would have pre and post measurements for vegetable intake, BMI z-scores, and waist circumference but only 60 children per school for blood glucose and insulin values. **Table 2** presents the minimum number of schools needed for power of 80% and 90% for the children's primary outcomes using a type I error of 0.05 and 0.01, a two-sided test, and assuming equal allocation between the two arms. The variance ( $\sigma^2$ ) within schools and the intraclass correlation coefficient (ICC) to estimate the sample size were obtained from the R21 pilot study. Therefore, with six schools and 60 children per school with blood draws, 360 children are needed, and given our preliminary data and attrition rates, we will have enough power to detect the effect size of a decrease in 2.13 mg/dL in fasting glucose. For the children, we will also have enough power to detect an effect size above 0.5 in vegetable (serv/d) intake, a decrease of 0.065 in BMI z-scores, a decrease of at least 0.02 cm in waist circumference, and a decrease of at least 12  $\mu$ U/ml in fasting insulin. **For Aim 2**, we estimate the power of this study for the parents using vegetable intake and availability from Castro et al using the same powers and type I error levels as we used for the

children as well as the R21 pilot data for the variance and ICC. Among the parents, we will have enough power to detect an effect size above 0.5 vegetable intake (serv/d) (**Table 2**).

**Data Analyses:** Summary statistics, graphical analyses, and frequency distributions will be used to describe the data between the intervention and control groups. Data will be transformed if needed. We will handle missing data using two primary approaches: multiple imputation and full information maximum likelihood estimation methods. Each method has potential biases and makes assumptions about the underlying basis for the missing data (e.g., missing at random-MAR) and other features of the data that are present. However, we have included enough baseline variables of the participants and at the follow-up visits to make the MAR assumption plausible. Without prior knowledge of the missing data process, we will have to explore the implications of applying different strategies. **For Aim 1:** We will test if the children and parents participating in Sprouts compared to control will have increased changes in average consumption of vegetable servings per day and decreased average changes in BMI z-scores, waist circumference, fasting glucose, and insulin using well-known statistical methods for cluster randomized trials. Several analytic strategies will be employed to determine the effect of the intervention on vegetable intake and many of the other primary outcome variables. We plan to conduct a two-stage nested analysis of variance model, which is a special case of the mixed effects linear regression model also known as a repeated measures analysis of variance model. The terms in the model include the true mean for the outcome variable, the fixed effects of the intervention arm, one random cluster effect (school), and the random error term. In this case, the schools (clusters) should be regarded as nested within the intervention arms and the students or parents within the school (clusters). We will model the pattern of covariance among observations as an unstructured variance–covariance matrix because of the small number of repeated assessments. We will also explore interaction effects between intervention group and selected covariates to determine whether the intervention was more effective for some covariates. For example, we will test whether the effectiveness of the intervention varied by age, gender, race/ethnicity, baseline BMI, percent free and reduced lunches, physical activity measures, class attendance, and wave of data collection. These tests will be considered as exploratory analysis and treated as hypothesis generating and interpreted with caution. The analytic approach for the secondary outcome measures (i.e., blood pressure, percent body fat, metabolic syndrome, adipocytokines, other dietary intake variables, and related dietary psychosocial behaviors) will involve a similar use of linear mixed models. Again, school will be modeled as a random effect nested within treatment arm, and treatment arm will be modeled as fixed effects. **For Aim 2:** To test the effects of the Sprouts intervention on changes in vegetable intake and availability and on related dietary behaviors in the parents, we will use similar and well-known statistical methods as described for Aim 1. As exploratory and secondary analyses, we intend to conduct structural equation modeling (SEM) with established mediational (and direct) effects, with and without the cluster effect variables, to examine how changes in behaviors, as well as program fidelity (attendance, dosage, delivery of intervention) impacts changes in main health outcomes. For the **Exploratory Aim**, we will conduct descriptive statistics on the collected pilot data of the sustainability strategies (qualitative and quantitative data obtained via structured interviews and focus groups) on both intervention and control schools. The unit of analysis will change, as these measurements will be collected on teachers, principals, GLCs, administration staff, district directors and staff. We will obtain pilot data on the differences between intervention and control schools on the following: number of curriculum lessons taught, use and maintenance of garden, successful components/strategies implemented to sustain program, and additional material/resources/training requested, etc. This pilot data will serve to consider future projects to sustain the program and for power and sample size purposes.

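### Table 2's school counts for vegetable intake, parents and insulin do not follow from their printed inputs, and its smallest glucose and BMI z counts overstate power, although 16 schools are not shown to be too few

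*Protocol*

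**What the plan says.** The Sample Size and Power Analysis paragraph (Protocol, section 5) presents Table 2 as the "minimum number of schools needed for power of 80% and 90% for the children's primary outcomes". Tests are two-sided at the 0.05 and 0.01 levels, with schools divided evenly between arms. Each column has an ICC, a variance and an effect. The footnote describes the variance as "variance within schools from pilot data", and the text repeats that the variance is the one within schools. The table header gives a "cluster average size of n=127 for diet, waist, BMI z-scores and 60 for glucose/insulin values per school", and 64 per school for parents.

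The text says that "with six schools and 60 children per school with blood draws, 360 children are needed", and that this suffices for a 2.13 mg/dL fall in glucose. It also claims enough power for "an effect size above 0.5 in vegetable (serv/d) intake", for 0.065 in BMI z, 0.02 cm in waist and 12 µU/ml in insulin, and for a vegetable effect above 0.5 in parents.

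Under Data Analyses, school is a random effect nested in arm. Under Recruitment, 16 schools are allocated, 8 per arm.

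**The concern.** Table 2 is the protocol's only sizing calculation, so a reader should be able to recover its counts from the inputs printed above them. Three of the six columns cannot be recovered. Two of these, vegetable intake and insulin, are among the five primary child outcomes; the third, parents, belongs to Aim 2.

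The variance symbol seems to mean different things in different columns. If it is mislabelled, anyone reusing it, for a sample-size check or a later trial, would be wrong by a factor of about 14 for vegetables (1.127/0.08).

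Separately, the smallest counts rest on comparisons of two or three schools per arm. There the normal approximation fails, and the text relies on one of these counts in words.

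**Working it through.** **Inputs (Table 2; columns taken in order, vegetables first and parents last, which the effects in the text confirm).** m is children or parents per school and d the effect.

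| Outcome | m | ICC | σ² | d |
|---|---|---|---|---|
| Vegetables | 127 | 0.071 | 0.08 | 0.500 |
| Glucose | 60 | 0.001 | 40.86 | 2.133 |
| BMI z | 127 | 0.002 | 0.05 | 0.065 |
| Waist | 127 | 0.019 | 0.005 | 0.020 |
| Insulin | 60 | 0.554 | 30.41 | 12 |
| Parents | 64 | 0.071 | 0.08 | 0.510 |

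**Formula.** Schools per arm = c × (z for α/2 + z for power)², with c = 2σ²[1+(m−1)ICC]/(m d²), rounded up and doubled. The squared sums are 7.849, 10.507, 11.679 and 14.879 for (α 0.05: 80%, 90%) and (α 0.01: 80%, 90%). Counts below are in that order.

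**Columns that reproduce.**
- Glucose: c = 2×40.86×1.059/(60×2.133²) = 0.317, giving 2.49/3.33/3.70/4.72 per arm, so 6/8/8/10. Exact.
- BMI z: c = 2×0.05×1.252/(127×0.065²) = 0.233, giving 1.83/2.45/2.73/3.47, so 4/6/6/8. Exact.
- Waist: c = 0.668, giving 12/16/16/20 against 12/16/18/22. An unrounded σ² of about 0.0052 to 0.0055 gives the listed row, so rounding explains it.

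**Vegetables and parents.**
- Vegetables as printed: c = 2×0.08×9.946/(127×0.25) = 0.0501, giving 0.39/0.53/0.59/0.75 per arm, so 2 schools in every cell.
- Parents as printed: c = 2×0.08×5.473/(64×0.2601) = 0.0526, giving 0.41 to 0.78, again 2 in every cell.
- σ² as strictly within-school (total 0.08/0.929 = 0.086): still 2 in every cell.
- σ² as between-school (total 0.08/0.071 = 1.127): vegetables 5.54/7.42/8.24/10.50, so 12/16/18/22; parents 5.82/7.79/8.65/11.02, so 12/16/18/24. All eight cells match.

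**Insulin (listed 14/20/24/30).** The design effect is 1+59×0.554 = 33.686.
- σ² as total: c = 0.237, giving 4/6/6/8.
- σ² as within-school (total 30.41/0.446 = 68.2): 10/12/14/16.
- σ² as between-school (total 30.41/0.554 = 54.9): 8/10/10/14.
- Any inputs at all: a count of 14 at 80% and α 0.05 requires c ≤ 7/7.849 = 0.892. A count of 24 at 80% and α 0.01 requires c > 11/11.679 = 0.942. Both cannot hold, so no combination of variance, ICC, cluster size and effect gives this row. A search using t quantiles, or one extra school per arm, found none either.

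**Degrees of freedom.** With school as a random effect, a comparison of k schools has k−2 df. Power comes from the noncentral t with noncentrality √(k/2c).
- Glucose, 6 schools: noncentrality √(3/0.317) = 3.08, critical value 2.776 on 4 df, power 64% (listed 80%).
- BMI z, 4 schools: noncentrality √(2/0.233) = 2.93, critical value 4.303 on 2 df, power 37% (listed 80%).
- t-based minimum counts: glucose 8/10/12/14; BMI z 8/8/10/12; waist 14/18/20/24; vegetables and parents, on the between-school reading, both 14/18/22/26.

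**Power at the planned 16 schools (14 df, two-sided 0.05).**

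| Outcome | Power |
|---|---|
| Glucose, 2.133 | 99.6% |
| BMI z, 0.065 | above 99.9% |
| Waist, 0.02 (σ² 0.0055 to 0.005) | 87 to 90% |
| Vegetables, 0.5 (between-school reading) | 88% |
| Parents, 0.51 (between-school reading) | 86% |
| Insulin, 12: total / between / within | above 99.9% / 98% / 95% |

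Table 2 lists 16 schools as giving 90% for vegetables and for parents.

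**The case against.** The strongest reply is that nothing claimed at the actual size fails. The text promises enough power, not 90%, and at 16 schools every stated effect clears 80%. Taken at face value, the vegetable, parent and insulin counts are larger than their printed inputs need. Four and six schools describe trials nobody will run, since blood draws are planned at 60 per school across 16 schools. Normal quantiles are an ordinary planning approximation, and the protocol fixes no degrees-of-freedom method.

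Much of this stands, and it bounds the consequence. It does not remove the point: the inputs and counts disagree on the page, one row is arithmetically impossible, and the six-school sentence is an explicit statement of adequacy that is wrong for the planned nested analysis.

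A reader might go further and infer that insulin was really sized for an effect of 6, which with variance 30.41 gives 16/20/24/30 and only 77% power at 16 schools. The documents do not support this. An effect of 6 appears nowhere, table and text agree on 12, and only three of the four cells match. An effect of 9 with total variance 68.2 fits the same three cells, so back-solving does not identify the source. Nor can one say that every column used normal quantiles: that is not shown for insulin.

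**Conclusion.** The point holds as an error of reporting and arithmetic in Table 2. The vegetable and parent counts contradict the variance label; the insulin row follows from no single set of inputs; and the six-school glucose and four-school BMI z entries carry about 64% and 37% power instead of 80%.

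At 16 schools the loss for vegetables and parents is 2 to 4 points against the listed 90%. The trial is not shown to be too small for any stated effect.

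This rests on three assumptions: the standard equal-cluster formula, supported by the exact match in eight glucose and BMI z cells; k−2 df for the arm comparison; and, for vegetables and parents at 16 schools, 0.08 as the between-school component. That last reading is inferred from the counts and has not been checked against the pilot data.

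**What to change.** 1. Check 0.08 against the pilot data and state which variance component it is, or print the total variance. The 1.13 derived here is back-calculated and should not be inserted unchecked.
2. Recheck the insulin variance, ICC, effect and all four counts against the pilot data and correct whichever is wrong, without presuming that the 12 is the error.
3. Rerun Table 2 with t quantiles on k−2 df.
4. Replace the sentence on six schools and 360 children with the power, or the detectable effect, at the actual 16 schools for each outcome.

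The cost is one table and two sentences. Some stated powers become slightly less favourable, and the number of schools is unchanged.
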